# A Comparison of the Efficacy of Immediate *Versus* Delayed Frozen–Thawed Embryo Transfer on the Ongoing Pregnancy Rate After a Failed IVF Attempt: Study Protocol for a Randomized, Non-Inferiority, Parallel-Group, Controlled Trial

**DOI:** 10.3389/fendo.2021.603158

**Published:** 2021-02-18

**Keywords:** randomized controlled trial, pregnancy, *in-vitro* fertilization, time interval, frozen–thawed embryo transfer

## Abstract

**Introduction:**

In clinical practice, the ideal time at which to perform a Frozen–thawed Embryo Transfer (FET) after a failed *In-vitro* Fertilization-embryo Transfer (IVF-ET) is still unclear to most practicing physicians. In addition, physicians often delay the introduction of FET due to concerns on the possible residual effects of ovarian hyperstimulation, which may interfere with the regular menstrual cycle. Moreover, given that most of the published studies on the topic are retrospective with contradictory findings, it is crucial to provide evidence-based randomized control guides for clinical practice.

**Methods/analysis:**

The study is a randomized, non-inferiority, parallel-group, controlled trial that will enroll a total of 732 women undergoing their first FET after a failed fresh embryo transfer (ET) cycle. The participants will then be randomized into two groups based on a computer-generated randomized list. The two groups include: (i) an immediate group were FET will be carried out during the first menstrual cycle after a failed fresh ET cycle and (ii) a delayed group where FET will be carried out during the second menstrual cycle after a failed fresh ET cycle. Primary outcomes will be defined as viable pregnancies with fetal heartbeats, diagnosed through pelvic ultrasonography after twelve weeks of gestation.

**Ethics and dissemination:**

The study was approved by the Ethics Committee of the Assisted Reproductive Medicine at the Affiliated Hospital of Shandong University of Traditional Chinese Medicine (SDTCM/E-2020.2.01). In addition, written informed consent will be obtained from all the participants before the study. The results of this trial will be disseminated in a peer-reviewed journal.

**Discussion:**

Currently, there is no consensus with regard to the duration after which the effects of ovarian stimulation are observed after a failed fresh ET and the optimal time required to begin FET. Moreover, no randomized controlled trial exists that compares the ongoing pregnancy rates after immediate versus delayed FET following a failed fresh ET cycle. Therefore, it is important to conduct a well-designed randomized trial to determine whether it is necessary to delay FET for at least one menstrual cycle after the failure of fresh ET.

**Clinical Trial Registration:**

ChiCTR2000033313 (http://www.chictr.org.cn/enIndex.aspx).

## Highlights

The present study is the first randomized controlled trial to attempt to accumulate significant clinical evidence and draw conclusions with regard to the ideal time to conduct FET after a failed fresh embryo transfer cycle.The current protocol includes participants aged 21–44 years, undergoing their first FET after the fixed GnRH antagonist protocol with standard Controlled Ovarian Stimulation (COS) in the IVF/ICSI procedure. The results obtained will therefore be able to reflect the situation in a majority of women in the infertile population.However, it will be impossible to blind the allocation of intervention measures to the participants, physicians, and researchers.The sample size calculation in the current study may also not be able to detect smaller differences in the ongoing pregnancy rates of 10% between the immediate and delayed groups.

## Introduction

Since the early success achieved with FET three decades ago, embryo deferrals and cryopreservation have become an increasingly essential aspect of IVF treatment (1). In addition, women whose attempt at pregnancy failed after a fresh embryo transfer (ET) during a stimulated IVF cycle, often opt to immediately proceed with FET in order to get pregnant as soon as possible. However, the difference between fresh or frozen embryo transfers with regard to perinatal outcomes has been a subject of controversy. Notably, FET cycles have previously been associated with lower rates of *antepartum* hemorrhage (2), pre-term birth, ectopic pregnancy (3–6) and low birth weight (7–10). Nonetheless, FETs have been linked to higher rates of placental/hypertensive complications (5), large-for-gestational-age infants (5, 11) and inconclusive perinatal mortality rates (2, 11). Therefore, given the setbacks, most researchers are currently skeptical on the overall benefits of FET (12–15). In addition, physicians are generally questioned on ovarian hyperstimulation and the long-term effects on subsequent treatment (16). As such, FETs are often postponed in an attempt to minimize the possible residual effects of ovarian hyperstimulation on endometrial receptivity (17). However, existing literature on the area is largely scarce (18, 19) although deferrals by physicians even with the best of intentions, might frustrate couples.

Presently, limited evidence exists on the “perfect” timing for FET following a failed-fresh stimulated IVF cycle. Notably, two options can be considered following a failed-fresh cycle: the first one would be to perform FET during the first cycle (an immediate embryo transfer) while the other option would be to postpone for least one menstrual cycle (a delayed embryo transfer). In addition, two studies on failed fresh IVF showed no differences in the live birth rates or clinical pregnancies between delayed and immediate FET (20, 21). In contrast, Mass K et al. suggested that patients should not postpone FET after fresh ET failure. Additionally, Volodarsky-Perel et al. reported that FET should be postponed for at least one menstrual cycle, after a failed-fresh cycle (17, 22). Therefore, given the contradictory reports, it is necessary to provide evidence-based randomized control guides for clinical practice. Consequently, the present randomized clinical trial aims to compare the ongoing pregnancy rate after immediate *versus* delayed FET following a failed-fresh cycle. It is hypothesized that the ongoing pregnancy rates of the two options will be comparable. The following article is presented in accordance to the SPIRIT reporting checklist.

## Methods and Materials

### Study Design

The study is a controlled single-center, randomized, parallel group, non-inferiority clinical trial conducted at the Affiliated Hospital of Shandong University of Traditional Chinese Medicine (TCM). An overview of the study visits is shown in **Table 1**, and the study flow chart is highlighted in **Figure 1**.

**Table 1 T1:** Schedule of the study process (SPIRIT Figure).

	Study Period				
	Enrollment	Allocation	Post allocation		
Time point*	1st visit	2nd visit	3rd visit	Pregnancy visit	Follow-up visit
Preconception counselling	**√**	**√**	**√**	**√**	**√**
Eligibility screen	**√**				
Informed consent	**√**				
Questionnaire	**√**	**√**			
Laboratory index measurement (oocyte, zygote, embryo, *etc.*)	**√**				
Serological test for pregnancy		**√**	**√**	**√**	
Allocation (immediate FET or delayed FET)		**√**	**√**		
Menstrual cycle records			**√**		
Transvaginal ultrasound for pregnancy outcomes			**√**	**√**	**√**
Perinatal and neonatal outcomes records				**√**	**√**

**Figure 1 f1:**
[figure not shown]
The study flowchart.

### Participants

The participants will consist of women (who met the inclusion criteria) and their partners receiving IVF or ICSIs, recruited by physicians in the fertility clinics. Given that the number of patients who make daily visits is sufficient, there will be no need for additional strategies to ensure adequate recruitment. Thereafter, the participants will undergo detailed counseling and explanation from the doctors after which they will be required to sign the informed consent forms. Following this, eligible participants will be randomly allocated to either a delayed or an immediate group.

### Inclusion Criteria

Participants must be <44 years of age at the time of IVF/ICSI treatment.Participants should have undergone an initial FET cycle after a failed fresh ET in IVF/ICSI.Participants should be undergoing IVF/ICSI with a standard ovarian stimulation protocol.Participants should have at least one frozen embryo remaining for transfer.

### Exclusion Criteria

Individuals with a Body Mass Index (BMI) ≥28 kg/m^2^.Those using the natural cycle or mild stimulation for IVF/ICSI treatment.Individuals with severe hyperstimulation ovarian syndrome during controlled ovarian stimulation.Those with a history of unilateral oophorectomy or recurrent pregnancy loss, defined as two or more spontaneous abortions.Acceptors of donated oocytes or performed either *In vitro* Maturation (IVM) or blastocyst biopsy for Preimplantation Genetic Diagnosis (PGD) or Preimplantation Genetic Testing for Aneuploidies (PGT-A).Those previously diagnosed with congenital (*e.g*. mediastinal uterus and double uterus) or acquired (*e.g.* submucosal myoma and adenomyosis) uterine abnormalities.Presence of a non-surgically treated hydrosalpinx or endometrial polyp and an ovarian endometriosis cyst requiring surgery, during ovarian stimulation.

Standard and mild stimulation in the study will be defined according to published ovarian stimulation terminologies for IVF (23). On the other hand, endometriosis will be diagnosed and classified according to guidelines by the European Society of Human Reproduction and Embryology (ESHRE) (24). Additionally, the Ovarian Hyperstimulation Syndrome (OHSS) will be classified and diagnosed according to guidelines by the Royal College of Obstetricians and Gynecologists (25).

### Randomization

Women undergoing the first FET cycle after a failed-fresh cycle will be randomized into two groups (immediate and delayed) according to a computer-generated randomization list. Randomization will be conducted on the day of the negative blood *β*-hCG test (fourteen days after fresh embryo transfer), for participants with a failed-fresh ET. In addition, randomization will be conducted by the study nurse blinded from the entire recruitment and clinical management of the participants through random number generation and grouping using the SPSS software (Version 26.0, IBM Corp., Armonk). Moreover, the same project nurse will prepare the randomization arm by placing them into opaque envelopes for subsequent use. Finally, participants will be randomized according to the opaque envelopes into one of two groups: 1) The immediate group in which FET will be performed after the first menstrual cycle following the failed-fresh cycle; 2) The delayed group in which FET will be performed after two or more menstrual cycles following the failed-fresh cycle.

### Blinding

Due to the nature of the study, it will be impossible to blind the participants and researchers. However, the embryologist, carrying out the assessments (embryo quality test) will be blinded to the intervention.

### Interventions

Participants will undergo the IVF/ICSI treatment as clinically indicated. In addition, fixed GnRH antagonist (GnRH-ant) (cetrorelix; Merck Serono, Darmstadt, Germany) protocol will be employed with 150–450 IU/day of recombinant FSH (Puregon, MSD, Courbevoie, France; Gonal-F, Merck-Serono, Lyon, France). Additionally, the doses of gonadotropin will be determined based on the characteristics of individual patients. Thereafter, oocyte retrieval will be conducted under ultrasound transvaginal guidance, 34–36 h after triggering with GnRH-a (Triptoreline, Decapeptyl, Ipsen, France) or recombinant hCG (rhCG, Ovitrelle, Serono, France). Additionally, the BD Falcon IVF medium (Becton, Dickinson and Company, Franklin Lakes, NJ, USA) will be used to collect the oocytes and perform embryo culture at 6% CO_2_, 5% O_2_ and 37.0°C (C200 CO_2_ Incubator, Labotect Labor-Technik-Göttingen GmbH, Göttingen, Germany). After this, oocytes will be fertilized based on the semen quality of individual participants’ partner, using either conventional insemination or ICSI following the standard protocol. Normal fertilization will then be assessed (a second polar body and two pronuclei) after 16–18 h of insemination or ICSI. Notably, an embryo with at least seven blastomeres (grades one and two) on the third day after oocyte retrieval will be defined as good quality. In addition, embryos with fragments <50% will be frozen. According to the standard protocol, all “good” embryos will be vitrified using the cryopreservation method on the third day. Furthermore, patients with more than six good-quality embryos on the third day will be counseled for extended blastocyst and culture transfer.

In addition, a failed-fresh cycle will be defined as a negative *β*-hCG test, fourteen days after fresh embryo transfer. Participants will then be randomized to immediate *versus* delayed groups by specially assigned nurses on the material day. They will also be advised on whether to wait for one or more menstrual cycles after the failed embryo transfer, before the next visit. Moreover, all participants will receive the same treatment before and after the subsequent visit, and there will be no other relevant interventions or concomitant care during the clinical trial. The nurses will inform patients before enrollment that once they are assigned to a group, they will not be able to change unless an unexpected event necessitates the cancellation of embryo transfer.

Furthermore, the participants’ stress and anxiety levels will be measured using a standard questionnaire before randomization and at the time of commencing FETs. In addition, the Chinese State-Trait Anxiety Inventory will be used to measure the patient’s anxiety levels (26).

On the other hand, Hormone Replacement Treatment (HRT) will be used for endometrial preparation. In addition, treatment with Estradiol valerate will commence on the third day of the menstrual cycle at a dose of 4–6 mg/day for 10–12 days. Moreover, vaginal progesterone (8% Crinone, Merck-Serono, Switzerland) will be administered at a dose of 90 mg per day, after the endometrial layer reaches a thickness of 8 mm as revealed by pelvic ultrasound scanning. FET for day three embryos will also be scheduled on the fourth day after commencing treatment with vaginal progesterone. Furthermore, at least one embryo with the best morphology, will be transferred using a soft embryo-transfer catheter with the guidance of ultrasound. Finally, the serum *β*-hCG levels will be checked fourteen days after FET.

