### Statistical Analysis and Sample Size Calculations

#### Estimation of Sample Size

The PASS software version 11.0 (NCSS, LLC. Kaysville, Utah, USA.) will be used to calculate the sample sizes for both groups. Notably, the ongoing pregnancy rate per FET was about 30% based on data from our reproductive center, at the time of the trial design. The calculation revealed that 329 women were to be included in each trial group to provide an 80% power to detect a minimally important absolute difference of 10% points between the immediate and delayed groups for the primary outcome of ongoing pregnancy (40 *vs* 30%) at a two­sided *α* level of 0.05. However, the trial plans to include 732 women, with 366 participants in each arm in order to account for an expected 10% loss to follow-up.

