#### Data Analysis

The intention-to-treat analysis will be used to examine differences in the ongoing pregnancy rate and other secondary outcomes in the two treatment arms during primary analysis. In addition, multiple imputations will be used to process missing values in the data. The demographic characteristics of the two groups will also be compared. Notably, categorical variables will be compared using χ2 analysis while the Student’s t-test will be used to compare quantitative variables. Moreover, multivariable logistic regression will be used to adjust for potentially confounding factors and results, if the randomization fails to achieve two balanced groups. Such factors will include the COH protocol, number of good-quality embryos, female age at oocyte-retrieval day, number of transferred embryos, retrieved oocytes, and quality of the transferred embryos. All statistical analyses will be performed using the SPSS version 26.0 software and a p-value <0.05 will be considered to be statistically significant.

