## Discussion

In daily clinical practice, deciding on when to perform FET after a failed oocyte retrieval-ET procedure is often a dilemma. In addition, most of the patients prefer to continue treatment by postponing the transfer of their remaining cryopreserved embryos.

In a small retrospective cohort study (n = 129), Volodarsky-Perel et al. found that postponing FET by at least one menstrual cycle after a failed fresh ET was beneficial for pregnancy outcomes compared to immediate FET. This was observed if a preceding long GnRH-agonist protocol for COS was used and if an artificial preparation was indicated for FET (22). However, these results were contrary to those recently reported by a large retrospective study (n = 1,183) which revealed a similar clinical pregnancy rate in first FET cycles that were performed immediately (≤22 days) or later on (>22 days) after oocyte retrieval from the preceding failed fresh ET (21). The study concluded that deferring FET may unnecessarily prolong the time to pregnancy. Nevertheless, the results were drawn from cycles that followed failed Fresh ET using the ovarian stimulation-GnRH-ant protocol. All in all, the contradictory results from the two studies may have been due to the different protocols used for ovarian stimulation, *i.e.* GnRH analog in the failed fresh ET and in the subsequent first FET cycle.

The purpose of this randomized controlled trial is not necessarily to confirm the superiority or inferiority of immediate FET after the failure of fresh ET. On the contrary, it aims to assure both clinicians and patients that although fresh ET fails, immediate FET has no adverse effects on the eventual pregnancy outcomes, compared to delayed FET. As such, it may be beneficial in alleviating psychological pressure on patients and shorten the Time to Pregnancy (TTP) and is therefore worth trying.

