## Trial Status and Peer Review

This trial is at Version 1.7, 28/5/2020 (ChiCTR). The study was designed on the 10^th^ of May, 2020, and the first participants were randomized on the 15^th^ of October, 2020.

The actual study start date was 1 June 2020, and it is anticipated to end on 31 May 2021. In addition, recruitment began on 15 June 2020, and it was anticipated to end on 15 October 2020. At the time of the manuscript preparation, the study will have recruited 310 infertile women and recruitment currently is ongoing. This study is externally peer-reviewed and does not include commission.

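### A change of group is allowed after a cancelled transfer, and only intention-to-treat is named; if cancelled immediate-arm women are transferred later, this can favour a non-inferiority claim

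*Protocol article*

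**What the plan says.** Study Design describes a "randomized, parallel group, non-inferiority clinical trial". Under Interventions, nurses tell women before enrolment that after allocation "they will not be able to change unless an unexpected event necessitates the cancellation of embryo transfer". The text does not say whether a cancelled woman is transferred again within the trial, or in which arm she is then counted.

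Data Analysis states: "The intention-to-treat analysis will be used to examine differences in the ongoing pregnancy rate and other secondary outcomes". No other analysis set is named.

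The groups are defined in two ways. The abstract puts immediate transfer in the first cycle and describes "a delayed group where FET will be carried out during the second menstrual cycle after a failed fresh ET cycle". Randomization puts immediate transfer after the first cycle and says of the delayed group that "FET will be performed after two or more menstrual cycles following the failed-fresh cycle".

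The Discussion gives the aim as assurance that "immediate FET has no adverse effects on the eventual pregnancy outcomes", compared with delayed transfer.

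**The concern.** In a non-inferiority trial, anything that makes the arms look alike can help the claim. A cancelled transfer can only be rescheduled later. In the immediate arm, a postponement of one cycle turns immediate timing into delayed timing under either pair of definitions. In the delayed arm, a postponement stays late; it can never become a first-cycle transfer. Crossover caused by this exception therefore runs in one direction only, towards the comparator.

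The route is plausible. Interventions starts progesterone only once the endometrium reaches 8 mm and gives no rule for women who do not reach it. The stake is a false reassurance about immediate transfer, which is the statement the trial is meant to support.

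**Working it through.** **The plan's own figures.** Estimation of Sample Size gives 329 per arm, raised to 366 for 10% loss: 329 / 0.9 = 365.6, so 366 per arm and 732 in total. The inputs stated there (40% versus 30%, two-sided 5%, 80% power) give 356 per arm, not 329. A non-inferiority calculation with 30% in both arms, a 10-point margin and one-sided 2.5% gives (1.960 + 0.842)² × 2 × 0.30 × 0.70 / 0.10² ≈ 330. That mismatch is a separate matter. Here it only makes a 10-point margin a reasonable assumption; the section itself calls the figure "a minimally important absolute difference of 10% points between the immediate and delayed groups", not a margin.

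**Inputs.**
- From the article: 366 per arm (329 after loss); 30% ongoing pregnancy, used here for the delayed arm.
- Assumed: margin 10 points; immediate transfer truly worse by exactly that margin (20%); a share c of 3%, 8% or 13% of the immediate arm crosses over (366 × c = 11, 29 or 48 women); crossovers reach an ongoing pregnancy rate r.

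**Formulas.**
- Immediate-arm ITT rate: p = (1 − c) × 0.20 + c × r.
- SE = √[p(1 − p)/n + 0.30 × 0.70/n].
- Risk of a false claim: Φ[(p − 0.30 + 0.10)/SE − 1.96].

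**One line in full** (c = 8%, r = 30%, n = 366): p = 0.92 × 0.20 + 0.08 × 0.30 = 0.208. The gap is 9.2 points. SE = √[(0.1647 + 0.2100)/366] = 0.0320. The risk is Φ(0.008/0.0320 − 1.96) = Φ(−1.71) = 4.4%.

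| Rate r among crossovers | c = 3% | c = 8% | c = 13% |
|---|---|---|---|
| 30% (as delayed arm) | 3.1% | 4.4% | 6.0% |
| 25% | 2.8% | 3.3% | 3.9% |
| 20% (as immediate arm) | 2.5% | 2.5% | 2.5% |
| 15% | 2.2% | 1.8% | 1.5% |

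In the first row the gap shrinks from 10 points to 9.7, 9.2 and 8.7. With 329 per arm that row is 3.1%, 4.2% and 5.7%.

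**Women never transferred.** Under ITT, a cancelled woman with no later transfer counts as not pregnant. If one third of cancelled women are in this position and the rest reach 30%, the average is 2/3 × 30% = 20% and the effect vanishes. With true rates of 30% in both arms, 10% such women in the immediate arm alone give 0.90 × 30% = 27%, a 3-point shift against non-inferiority.

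**Requiring two analyses to agree.** Simulation (400,000 trials per setting, r = 30%, 366 per arm, ITT and as-assigned both required to meet the margin) returns the false-claim risk to about 2.4%. With 30% in both arms, power falls from 84.0% for ITT alone to 82.5%, 81.2% and 80.0% at the three crossover shares. With 329 per arm it falls from about 80% to 78.3%, 77.0% and 75.5%.

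**Selection in the as-assigned set.** It drops rescheduled women from the immediate arm only. If the arm average is 30% and the 8% cancelled would reach 20%, the remainder has (0.30 − 0.08 × 0.20)/0.92 = 30.9%, a gain of 0.9 points that favours non-inferiority.

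**The case against.** The strongest case against has four parts.

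- **Analysis sets are often left to the SAP.** This is a condensed article, and naming ITT as primary does not exclude supportive analyses. This stands so far as the absence of a second analysis alone would be no finding. What remains is that the article itself fixes a conduct rule opening a change of group.
- **ITT fits the aim.** The Discussion speaks of eventual pregnancy outcomes, and a woman who tries the first cycle, is cancelled and is transferred in the next belongs to the strategy of immediate transfer. This stands. A reader might infer that ITT is the wrong primary analysis; the documents do not support that.
- **The direction is not certain.** A reader might infer that the exception necessarily pushes towards non-inferiority. The text does not say that cancelled women are transferred again, and women cancelled for poor endometrial response may have a worse prognosis. This also stands. One-way crossover holds for changes caused by cancellation, but the resulting bias is conditional.
- **Timing may already be recoverable.** Table 1 schedules menstrual cycle records, and Data Entry and Quality Control collects frozen-transfer data on the transfer day. That makes the fix cheaper but does not say how such women are handled.

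A reader might also infer that agreement of both analyses should be mandatory. The selection and power figures above argue against it.

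**Conclusion.** The point holds in conditional form. The exception permits a change of group, any crossover it causes runs only from immediate to delayed timing, and the named analysis does not show its effect. If immediate transfer is truly 10 points worse, the assumed margin is 10 points and 3% to 13% of the immediate arm cross over, the false-claim risk is at most 3.1% to 6.0% instead of 2.5%. That upper end requires every crossover to be transferred and the group to match the delayed-arm rate. The effect is nil if crossovers do no better than the immediate arm, and it reverses if they do worse or are not transferred. The actual size cannot be known from the article, because margin, cancellation rate and crossover success are all unstated. This is a modest weakness worth closing, not an error in choosing ITT.

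**What to change.** - **Interventions:** replace the exception with: *Allocation does not change if a transfer is cancelled; any later FET outside the assigned timing is recorded with its date and reason.*
- **Data Analysis:** keep ITT, with all randomised women in their assigned arm, as the primary analysis. Add a pre-specified supportive analysis of women transferred as assigned, adjusted for the prognostic factors already listed in that section and reported beside ITT. State that disagreement between the two limits the non-inferiority conclusion.
- **Abstract and Randomization:** use one definition of each group throughout, first cycle versus second or later cycle.

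The cost is small: wording changes and a little more analysis, with no new visits or scans. The article says that by the time of writing "the study will have recruited 310 infertile women", so cancellation dates and reasons must be retrieved for them, and the amendment made without looking at outcomes by arm. The supportive comparison is not randomised, because it excludes rescheduled women from the immediate arm only. It should therefore not be a mandatory co-primary, which would also cost about 3 points of power at 8% crossover (84.0% − 81.2% = 2.8).
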